## Abstract

**Background:**

Thousands of Rohingya refugee mothers at the world’s largest refugee camp located in Bangladesh are at risk of poor mental health. Accordingly, their children are also vulnerable to delayed cognitive and physical development.

**Objective:**

The aim of this study is to evaluate the effectiveness of an integrated care package in reducing the prevalence of developmental delays among children aged 1 year and improving their mothers’ mental health status.

**Methods:**

This is a parallel, two-arm, single-blind, cluster randomized controlled trial (cRCT). A total of 704 mother-child dyads residing at the Kutupalong refugee camp in Cox’s Bazar, Bangladesh, will be recruited from 22 clusters with 32 mother-child dyads per cluster. In the intervention arm, an integrated early childhood development and maternal mental health package will be delivered every quarter to mothers of newborns by trained community health workers until the child is 1 year old. Our primary outcome is a reduction in the prevalence of two or more childhood developmental delays of infants aged 1 year compared to the usual treatment. The secondary outcomes include reduced stunting among children and the prevalence of maternal depression. We will also assess the cost-effectiveness of the integrated intervention, and will further explore the intervention’s acceptability and feasibility.

**Results:**

At the time of submission, the study was at the stage of endpoint assessment. The data analysis started in December 2020, and the results are expected to be published after the first quarter of 2021.

**Conclusions:**

This study will address the burden of childhood developmental delays and poor maternal mental health in a low-resource setting. If proven effective, the delivery of the intervention through community health workers will ensure the proposed intervention’s sustainability.

**Trial Registration:**

ISRCTN Registry ISRCTN10892553; https://www.isrctn.com/ISRCTN10892553

**International Registered Report Identifier (IRRID):**

DERR1-10.2196/25047

## Introduction

Rohingya refugees settled in Bangladesh are one of the largest groups of refugees in the world [1]. Cumulatively, by 2019, approximately 911,566 Rohingya refugees settled in both refugee camps designated by the government as Forcibly Displaced Myanmar Nationals [2]. Among the camp residents, 52% are women, 23% of whom are within reproductive age [3].

These refugees residing in the camps live in drastic situations and suffer from hunger, poverty, lack of safety, and appropriate access to health services [3]. The mental health status of Rohingya refugee women has been reported to be poor, which could be due to prolonged exposure to violence, trauma, and stress of living under terrible circumstances [4]. Maternal mental health is a crucial factor in ensuring healthy child development [5]. However, women who have experienced a traumatic event in their lives, as is the case for refugees, are at higher risk of postpartum depression, which can impact the growth and nutrition [6] and development of their child [7], as childhood development is mediated by mothers’ responsive feeding and caregiving skills. Moreover, prolonged exposure to psychosocial risks such as maternal depression, violence, and lack of stimulation can profoundly affect children’s health and cognitive development under the age of 2 years [8]. Studies have shown that at least 2% of the total refugees who are children (approximately 17,200) aged less than 1 year [9] are at risk of delayed development at the refugee camps.

Health care barriers faced by refugees continue to increase the risk of delayed child development and poor mental health for women [10]. Only 10 hospitals currently serve refugee settlements with an allocation ratio of 1 per 130,000 people. The health care systems are overburdened, short-staffed, and lack the necessary resources and infrastructure to provide adequate care, and have been reported to show significant gaps in treatment available for mental health and child development care. These health care challenges indicate the need to evaluate a service delivery model for early child development that will help support the health care providers with effective, scalable, and cost-effective alternatives to promote the child development and maternal mental health of refugees [11]. Integrated childhood development care within maternal, neonatal, and child health services has already proven to be effective in preventing developmental delays for children 2 years of age in a similar context [12,13].

To address the challenges highlighted above, this study has the objectives to: (1) evaluate the effectiveness of an integrated care package in reducing the prevalence of two or more developmental delays among infants aged 1 year and improving childhood stunting compared to the usual treatment, (2) evaluate the effectiveness of the integrated care package in reducing maternal depression, (3) explore the cost-effectiveness of the integrated care package in reducing childhood developmental delays, and (4) perform a mixed method process evaluation study to explore the acceptability and feasibility of the intervention for both the providers and participants.

## Methods

### Study Design, Settings, and Participants

We will use a parallel arm, single-blind, cluster randomized controlled trial (cRCT) design [14] to evaluate the integrated and contextualized package's effectiveness in reducing childhood developmental delays compared to the usual treatment.

The study will be performed in the Kutapalong Rohingya refugee camp located in Cox's Bazar, Bangladesh, selected based on its size and distance from the district city and ease of communication. The Kutupalong refugee settlement is a cluster of 20 camps, most of which are adjacent to each other. Each camp has definite boundaries and segments called “blocks.” Two blocks are combined to form a cluster for randomization in this study.

The research participants will be 704 mother-child dyads recruited from the 22 clusters in the Kutupalong refugee camp. The inclusion criteria for mother-child pairs are that the child should be less than or equal to 6 weeks old, live with their biological mother, had a gestational period of at least 36 weeks, and weighed at least 2.5 kilograms at birth. Children with congenital abnormalities and mothers that have to move out of the area during the study period will be excluded from the trial. Participation of mother-child dyads in the study will be required for 12 months.

### Procedures

#### Randomization and Masking

To minimize the risk of contamination between research participants, the randomization unit will be a cluster comprising two blocks. Blocks are geographical areas with defined boundaries in refugee camps. A sampling frame of eligible blocks within camps in the study site will be drawn before randomization using the population data and live birth record rates. Eligible clusters will be randomized before the recruitment of research participants from each cluster. The clusters taking part in the study will be randomized to the intervention or control arm by an independent statistician on a 1:1 allocation ratio. SAS PROC PLAN will be used to generate the randomization sequence code.

Given the nature of the intervention, it will be impossible to blind participants to the treatment allocation status. However, the assessment team, principal investigators, and the trial statistician will be blind to clusters’ allocation status.

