#### Package of Care in Intervention and Control Arms

The care package will be delivered by the community health workers (CHWs) identified from the selected clusters. CHWs having at least 10 years of formal education and willing to contribute to the community will be preferred for collecting data and delivering the intervention.

For standardization of research results, the control arm will be strengthened by providing a 2-day training to CHWs on recruitment of the mother-child dyads, administration of outcome measures, record-keeping, log maintenance, compliance, and communication. They will also be trained on taking anthropometric measurements to record the children’s height, weight, and mid-upper arm circumference (MUAC) every quarter. These inputs will be the same for the control and intervention arms.

In addition to the procedures mentioned above, CHWs in the intervention arm will be provided an additional 2 days of training on delivering the intervention to mothers. They will be trained on using necessary counseling skills while interacting with the mothers, such as empathy, rapport-building, trust, sympathy, privacy, mindfulness, and suggestion. They will also learn how to deliver counseling sessions to participants using a pictorial training flipbook with educative messages.

The integrated care package delivered in the intervention arm has been adapted and contextualized in consultation with international early childhood development and mental health experts. A logic model describing the intervention mechanism is presented in Figure 1.

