### Statistical Analysis

The findings of the study will be reported following CONSORT guidelines for cRCTs [14]. The data will be entered regularly after receiving the paper forms from the field, and then checked for missing data before the next visit scheduled in the clusters, allowing researchers to communicate with the CHWs to address such issues. Furthermore, we will follow the recommended methods for treating missing data per the guidelines of the outcome measures being used. Finally, we will analyze data using intention-to-treat analysis that handles any missing data at the endpoint. Descriptive statistics will be calculated for outcome variables and baseline characteristics of participants according to treatment arm to ensure the comparability of all outcomes across arms. Adjusted analysis and subgroup analysis will be based on covariates determined at baseline.

Data will be analyzed using cluster trials with relatively few clusters in each arm in IBM SPSS Statistics version 23. Crude analysis to estimate cluster-level proportions will be used for categorical outcomes. An independent sample *t* test to calculate the absolute difference in outcome proportions between the two study arms at the endpoint will be calculated with 95% CIs and significance values. For continuous outcomes, cluster-level outcome values based on the mean outcome scores in each cluster will be calculated, and an independent *t* test will be used to estimate the treatment effect as the mean difference in the cluster level outcome values between the two arms (control and intervention) at the endpoint, with associated 95% CIs and *P* values. A two-stage method will be used to adjust for confounding variables using a logistic regression model for individual-level outcome data. We will then calculate the covariate-adjusted difference residuals for each cluster by calculating the mean difference between observed and predicted outcomes. Independent *t* tests will be used to estimate the covariate-adjusted treatment effect as the risk difference in the cluster-level difference residuals between the two arms, with associated 95% CI and *P* values. No interim analysis of outcomes is planned.

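### Dyads are recruited after cluster allocation by health workers who know the arm, so enrolment can differ between arms, and the crude cluster-level comparison leaves any such difference in the estimate

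*Protocol article*

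**What the plan says.** The order of events is explicit in the protocol article, Randomization and Masking: "Eligible clusters will be randomized before the recruitment of research participants from each cluster". The frame drawn before randomisation is a list of blocks, built "using the population data and live birth record rates". No birth or dyad is fixed at that stage.

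Package of Care in Intervention and Control Arms says who recruits. Control-arm CHWs receive a "2-day training to CHWs on recruitment of the mother-child dyads, administration of outcome measures", among other tasks, and "These inputs will be the same for the control and intervention arms". The arms then part: "CHWs in the intervention arm will be provided an additional 2 days of training on delivering the intervention to mothers". The same section says that CHWs with enough schooling "will be preferred for collecting data and delivering the intervention".

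The roles kept blind under Randomization and Masking are the outcome assessors, the principal investigators and the trial statistician. CHWs are not listed, and participants are said to be impossible to blind.

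Study Design, Settings, and Participants sets numeric limits on infant age, gestation and birth weight. It also excludes mothers who will leave the area during the study.

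Statistical Analysis begins with the unadjusted comparison: "Crude analysis to estimate cluster-level proportions will be used for categorical outcomes", followed by a t test between arms. It then describes a two-stage covariate-adjusted version, based on baseline covariates that are not named. The article does not say which of the two decides.

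**The concern.** Randomising clusters balances the populations of the blocks in expectation. It does not balance the dyads enrolled from them if the person enrolling already knows the arm. In this design the person who finds and recruits the mother in an intervention cluster is trained to give her the counselling, and nobody can deliver counselling while blind to it. Three routes are open:

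- which eligible newborns are approached;
- which mothers agree;
- how the leaving-the-area exclusion is judged, since at enrolment it is a forecast.

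At stake is the primary comparison. If enrolled infants differ in risk between arms from the start, the difference at 12 months mixes that imbalance with the effect of the package. Blinded assessors protect the measurement of the outcome, not the make-up of the groups. Intention-to-treat preserves the groups as enrolled, including any imbalance formed at enrolment.

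**Working it through.** **Does the stated design create the exposure?** Three statements, taken together, settle this. Allocation comes before recruitment, and only blocks are listed beforehand. Recruitment is a CHW task in both arms. Intervention CHWs also deliver the package and are outside the blinded roles. That CHWs know the arm is an inference, but a firm one.

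**How large could the effect be?** The documents give no figure for selective enrolment, so the shifts below are assumptions shown as a range.

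Inputs from Sample Size Calculations: control risk 34%, intervention risk 20%, intracluster correlation (ICC) 0.12, 22 clusters at 1:1, 32 dyads per cluster, 10% attrition.

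- Planned effect: 34 − 20 = 14 points.
- Clusters per arm: 22 / 2 = 11. Enrolled per arm: 11 × 32 = 352, as stated.
- Completers per cluster: 32 × 0.9 = 28.8, taken as 29.
- Design effect: 1 + (29 − 1) × 0.12 = 4.36.

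Suppose the package does nothing, and selection alone lowers the intervention-arm risk from 34% to p. The standard error of the difference in mean cluster proportions is

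SE = √{[0.34 × 0.66 + p(1 − p)] × 4.36 / (29 × 11)}.

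For p = 0.30: √{(0.2244 + 0.2100) × 4.36 / 319} = 0.077, or 7.7 points. The two-sample t test has 22 − 2 = 20 degrees of freedom and critical value 2.086. Rejection comes from the noncentral t distribution with noncentrality (0.34 − p) / SE.

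| Assumed shift | p | SE (points) | Noncentrality | Two-sided rejection | Share of 14 points |
|---|---|---|---|---|---|
| 0 | 34% | 7.8 | 0 | 5.0% | 0% |
| 2 points | 32% | 7.8 | 0.26 | 5.7% | 2/14 = 14% |
| 4 points | 30% | 7.7 | 0.52 | 7.8% | 4/14 = 29% |
| 6 points | 28% | 7.6 | 0.79 | 11.6% | 6/14 = 43% |

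Beta-binomial simulation of the same test (100,000 runs, 29 per cluster) agrees: 5.1% with no shift, and 5.7%, 7.8% and 11.8% for the three shifts.

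The 4-point shift is about half a standard error, so the effect on the error rate is modest. The effect on the estimate is the full 4 points, whatever the p-value. If selection runs the other way, with higher-risk dyads enrolled in intervention clusters, a true 14-point reduction would appear as about 10.

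**How much selection would such shifts need?** Again by assumption, let half of eligible dyads be high-risk, and let the high-risk share enrolled be s lower in the intervention arm. The false reduction is s × (high risk − low risk).

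- Risks 44% and 24% (average 34%): s = 0.05 gives 0.05 × 20 = 1.0 point; s = 0.20 gives 4.0 points.
- Risks 48% and 20% (average 34%): s = 0.20 gives 0.20 × 28 = 5.6 points.

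A 2-point shift thus needs a 10-point difference in the high-risk share in the first case (0.10 × 20). A 6-point shift needs more than 20 points even in the second.

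**The case against.** The strongest reply is that the article condenses a fuller protocol. Consecutive enrolment, a screening log or a consent sequence that withholds the arm may be set out there, and CHWs in both arms are trained in log-keeping. This stands in part: the lack of an enrolment rule in the article is not evidence that none exists. The point rests instead on what is stated, namely the order of events, who recruits and who is blinded.

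Second, some recruitment after allocation is hard to avoid. Infants are at most 6 weeks old at entry, so many may be unborn when clusters are randomised. That also stands. The sequence is not an error in itself; it calls for safeguards.

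Third, a baseline comparison by arm and a two-stage adjusted analysis are already planned, and the choice of deciding analysis and covariates may sit in an analysis plan that is not shown. So a reader should not infer that the trial ignores imbalance. But adjustment reaches only measured covariates, and it protects the conclusion only if the adjusted result is the one relied on.

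Fourth, a reader might infer that the bias favours the intervention. Nothing in the documents supports a direction. A worker with a counselling package might approach the most engaged mothers or those most in need.

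Fifth, a reader might think that the birth-weight and gestation criteria add discretion. They are numeric thresholds and narrow it. The criterion that leaves room for judgement is leaving the area.

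**Conclusion.** The concern holds as an exposure to recruitment bias of unknown direction. The documents do not show that selective enrolment occurred, and the claim does not go that far. What they show is that the recruiter in intervention clusters knows the arm, that no dyad is fixed before allocation, and that neither blinded assessment nor the crude t test can correct the consequence.

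The size depends wholly on the assumed shift: over 2 to 6 points, the false-positive rate ranges from just above nominal to somewhat over twice nominal. These figures also rest on the stated ICC of 0.12, equal cluster sizes and no treatment effect. The bias in the estimate does not depend on the ICC and is the more important consequence. The matter deserves a change because the remedy is cheap and concerns the primary comparison, not because a large bias has been shown.

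**What to change.** **If enrolment is open:** state that each cluster enrols every eligible birth consecutively by birth date, and have CHWs log each eligible birth not enrolled, with the reason. This limits choice without needing a blinded recruiter. The article mentions only birth record rates, so it should not be assumed that a dated birth list already exists. Transferring consent to field coordinators is not an easy substitute: the Discussion reports a language barrier between them and the CHWs, and coordinators are not among the blinded roles either.

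**If enrolment is complete:** the Results section puts the trial at endpoint assessment, with analysis begun in December 2020, so this is the likely case.

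- Make the already planned two-stage covariate-adjusted cluster analysis primary. Use baseline covariates that the eligibility check implies are on record, for example birth weight, gestation and age at enrolment, and fix the list before unblinding. If allocation has already been revealed to the analyst, say so in the report.
- Report the crude analysis as supportive.
- Report eligible, approached and enrolled counts by arm where they were logged.
- State as a limitation that recruitment followed allocation, and that adjustment cannot remove unmeasured selection, such as selection on family engagement.

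**Cost:** a short log or a retrieval of existing logs, a few lines of text, and a little analysis work.

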#### Sample Size Calculations

For a two-sided hypothesis test with 22 clusters randomized at a 1:1 allocation ratio, and assuming an effect size of 0.35 with outcome proportions ranging from 34% to 20% for child development and from 30% to 15% for maternal depression, with 80% power, .05 significance, an intracluster correlation coefficient of 0.12, and accounting for 10% attrition, we will need 704 mother-child dyads (ie, 352 in each group), with 32 participants from each cluster on average. Findings from evidence synthesis indicate that early child development interventions usually yield small effect sizes [15], ranging from 0.2 to 0.4, per the Cohen criteria for effect sizes [16].

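### The stated 80% power does not follow from the protocol's own inputs: 22 clusters of 32 at ICC 0.12 give about 45% for the primary outcome and 56% for maternal depression

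*Protocol article*

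**What the plan says.** The Sample Size Calculations section gives a complete set of inputs. The design is "For a two-sided hypothesis test with 22 clusters randomized at a 1:1 allocation ratio", with 32 dyads per cluster on average. The targets are set by "assuming an effect size of 0.35 with outcome proportions ranging from 34% to 20% for child development and from 30% to 15% for maternal depression". The result is stated as "with 80% power, .05 significance, an intracluster correlation coefficient of 0.12, and accounting for 10% attrition, we will need 704 mother-child dyads", split as 352 per arm. The Abstract and the Study Design, Settings, and Participants section repeat 704 dyads and 22 clusters, and the Abstract also repeats 32 per cluster, so these figures are not a local slip.

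The Statistical Analysis section fixes the test. Proportions are computed for each cluster and the two arms are compared by an independent-samples t test, which leaves 22 − 2 = 20 degrees of freedom. No formula or software for the sample size is named.

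**The concern.** An ICC of 0.12 is large for clusters of about 30, because it multiplies the variance of an arm's proportion by more than four. With only 11 clusters per arm, it is doubtful that a 14-point difference could be found with 80% power. The single effect size of 0.35 adds to the doubt, since it is attached to two different pairs of proportions.

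What is at stake is how the result will be read. If the true power for the primary outcome is below one half, the trial is more likely to miss its own target effect than to detect it. A non-significant result reported beside a claim of 80% power would invite the reading that the package does not work, and the design could not support that.

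**Working it through.** **Inputs**, all from the Sample Size Calculations section except the test, which is from Statistical Analysis: k = 11 clusters per arm; 32 recruited per cluster; 10% attrition, so m = 32 × 0.9 = 28.8 analysed; ICC 0.12; two-sided alpha 0.05; 34% vs 20% and 30% vs 15%; cluster-level t test with 20 df. Equal cluster sizes are assumed.

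**Step 1. Try to reproduce 704.** Use the usual two-proportion formula, n per arm = (1.96 + 0.84)² × [p1(1−p1) + p2(1−p2)] / (p1−p2)², with (1.96 + 0.84)² = 7.849 before rounding.
- Primary: 7.849 × (0.2244 + 0.16) / 0.14² = 154 independent dyads per arm.
- Design effect: 1 + (28.8 − 1) × 0.12 = 4.336.
- Dyads to analyse: 154 × 4.336, about 667 per arm. Dyads to recruit: 667 / 0.9, about 742 per arm. The protocol states 352.
- Depression: 7.849 × (0.21 + 0.1275) / 0.15² = 118 per arm; × 4.336 is about 510; / 0.9 is about 567 per arm.

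The stated total is not reproduced for either outcome.

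**Step 2. Power of the stated design.** Effective n per arm = 11 × 28.8 / 4.336 = 316.8 / 4.336 = 73.06.

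| | 34% vs 20% | 30% vs 15% |
|---|---|---|
| SE of difference | √(0.3844/73.06) = 0.0725 | √(0.3375/73.06) = 0.0680 |
| Difference / SE | 0.14/0.0725 = 1.93 | 0.15/0.0680 = 2.21 |
| Power, t test, 20 df | 45.1% | 55.6% |
| Power, normal, unpooled | 48.8% | 59.8% |
| Power, normal, pooled | 47.8% | 58.5% |
| Beta-binomial simulation, 29 per cluster, 40,000 runs, t test | 44.9% | 55.8% |

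**Step 3. Could another reading give 80%?**
- No attrition (m = 32): 45.9% and 56.4% by t test.
- One-sided 0.05: 59–61% and 69–71%.
- 0.35 taken as a standardised difference: 52% (t) or 56% (normal), two-sided; 68% one-sided (normal).
- 0.12 read as a between-cluster coefficient of variation: about 94% and 98%.
- ICC of 0.012 (misplaced decimal): 91–93% and 97–98%.

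The first three fall short and the last two overshoot.

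**Step 4. The ceiling.** As m grows without limit, effective n per arm tends to k/ICC = 11/0.12 = 91.7. Power is then 54% (t) to 58% (normal) for the primary outcome, 65% to 70% for depression, and 62% to 66% for a standardised 0.35. No number of dyads per cluster gives 80% with 22 clusters at this ICC.

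**Step 5. What would be needed.**
- ICC giving 80% with 22 clusters: 0.031 (t) to 0.038 (normal) for the primary outcome; 0.052 to 0.061 for depression.
- Clusters giving 80% at ICC 0.12, by t test: 25 per arm (50 in all; 24 per arm gives 79.7%) for the primary outcome; 19 per arm (38 in all) for depression.
- Reduction detectable with 80% power from a control rate of 34%: to about 14%, or 20 points, by t test.
- Expected 95% CI half-width for the primary difference: 2.086 × 0.0725 = 15.1 points with the t quantile, or 1.96 × 0.0725 = 14.2 points with the normal. Both exceed the 14-point target.
- Unequal clusters, with an assumed size CV of 0.3: design effect 1 + (1.09 × 28.8 − 1) × 0.12 = 4.65, and primary power of about 43%.

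**Step 6. The effect size.** Cohen's h = 2·asin√p1 − 2·asin√p2 is 0.318 for 34% vs 20% and 0.364 for 30% vs 15%. The stated 0.35 lies between them and equals neither.

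**The case against.** The strongest reply is that 0.12 may be a misprint and the calculation used something smaller. That is possible, but the article gives no other value. The obvious slip, 0.012, does not return 80%, and no one ICC returns 80% for both outcomes. An ICC near 0.03 would give at least 80% for both, but nothing in the text supports it.

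A second reply is that the protocol also plans a two-stage covariate-adjusted analysis, which could remove some between-cluster variance. This is fair in principle. However, the power statement claims no such gain, and adjustment would have to bring the residual ICC down from 0.12 to about 0.03–0.04. Variable cluster sizes work the other way.

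Third, some consequences are limited to the primary outcome. The trial is more likely than not to detect its depression target (56–60%), and the ceiling and the number of clusters needed are less severe there. That stands, although depression is still well below 80%.

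Fourth, the 0.35 can be seen as one rounded figure for two outcomes, and the proportions are given explicitly. That also stands: it is loose wording and does not explain the gap.

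Finally, the analysis section already promises 95% confidence intervals. It does so, but does not say that a non-significant result will be interpreted through them, and the 80% beside them would still mislead.

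**Conclusion.** The power statement is wrong as written and must be corrected. On the protocol's own inputs, power is about 45% (49% by normal approximation) for the primary outcome and about 56% (60%) for maternal depression. This rests on 28.8 analysed per equal-sized cluster, ICC 0.12, the standard design effect and the planned unadjusted cluster-level t test. The conclusion does not depend on the choice between t and normal, on pooling, or on attrition. The shortfall lies in the number of clusters at this ICC, not in the number of dyads per cluster. The document cannot show whether the mistaken entry is the ICC or the power.

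**What to change.** Rewrite the Sample Size Calculations paragraph; enrolment stays as it is.

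- If 0.12 is the intended ICC, state that 22 clusters of 32 dyads with 10% attrition, analysed by a cluster-level t test, give about 45% power for 34% vs 20% and about 56% for 30% vs 15%. Add that the reduction detectable with 80% power is about 20 points from 34%.
- If a different ICC was used, print it with its source and with the formula or software. It should be the value used at the time of planning, not one solved backwards from 80%.
- Remove the single 0.35, or give the index for each outcome (0.32 and 0.36 as Cohen's h).
- Add that a non-significant result will be interpreted through the 95% confidence interval and the observed ICC, and not as evidence of no effect.

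The cost is wording only. If 0.12 stands, the stated power becomes less favourable.
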